## Abstract

**Background:**

For critically ill patients treated in intensive care units (ICU), two feeding strategies are currently being advocated, one by American/Canadian and the other by European expert guidelines. These guidelines differ particularly in the timing of initiating parenteral nutrition (PN) in patients for whom enteral nutrition (EN) does not reach caloric targets.

**Methods/Design:**

The EPaNIC trial is an investigator-initiated, non-commercial, multi-center, randomized, controlled, clinical trial with a parallel group design. This study compares early (European guideline) versus late (American/Canadian guideline) initiation of PN when EN fails to reach a caloric target. In the early PN group, PN is initiated within 24-48 hours after ICU admission to complete early enteral nutrition (EN) up to a calculated nutritional target. In the late PN group, PN completing EN is initiated when the target is not reached on day 8. In both groups, the same early EN protocol is applied. The study is designed to compare clinical outcome (morbidity and mortality) in the 2 study arms as well as to address several mechanistical questions. We here describe the EPaNIC study protocol and the statistical analysis plan for the primary report of the clinical results.

**Discussion:**

The study has been initiated as planned on august 01 2007. One interim analysis advised continuation of the trial. The study will be completed in February 2011.

**Trial Registration:**

ClinicalTrials (NCT): NCT00512122

## Background

### Nutritional support in ICU patients

It remains unclear whether artificial nutritional support beneficially affects outcome of critically ill patients. The route of administration, the delay before initiating such artificial nutrition, the amount of calories and possibly also the type of nutrient formula may be of importance [1-3].

As compared to parenteral nutrition (PN), enteral nutrition (EN), and early EN in particular, has been reported to be associated with less (infectious) complications [4-6], lower risk for pronounced hyperglycemia [5] and thus EN could be safer as well as cheaper. However, relying solely on EN often results in not achieving the caloric targets [7-9]. Indeed, even in stable intensive care unit (ICU) patients, early initiation of EN was associated with a high incidence of gastrointestinal intolerance and serious adverse events, such as regurgitation, suspected aspiration or colectasia, which necessitated stopping of EN [10]. Even after formal implementation of an evidence-based nutrition protocol in the ICU, the mean time to administering enteral feeding appeared to be about 3 days [1]. Furthermore, the mean percentage of caloric target achieved by day 4 was below 70% [1]. In addition, as physicians are unable to accurately predict which patient in the ICU will be resuming normal oral or enteral nutrition within one week after admission, the risk of underfeeding critically ill patients during the first week in ICU is substantial [11]. Indeed in many patients, solely relying upon EN has shown to result in underfeeding [7,8]. Underfeeding has been associated with an increased incidence of infection [12], and with other complications such as prolonged ventilation, prolonged length of stay and pressure ulcers [13,14]. In spite of such association between malnutrition and adverse outcomes, it has not been investigated in adequately powered randomized clinical trials (RCT) whether parenterally completing failing EN early in the course of critical illness provides an outcome benefit.

Combining PN with EN indeed represents a strategy to prevent such malnutrition, but has frequently led to overfeeding [7,15]. Overfeeding has been associated with increased risk of infection and metabolic disturbances, such as hyperglycemia, dyslipidaemia and liver dysfunction, as well as with prolonged mechanical ventilation [16,17]. Such a risk of overfeeding, however, could be prevented by using a computer-assisted feeding protocol via the patient data management systems (PDMS) currently in use in ICUs, as such system could remind physicians to reduce the PN supplement proportionally to the increase in enteral intake. Furthermore, a meta-analysis demonstrated that elevated blood glucose levels with early PN as compared with early EN may at least partially explain more infectious and non-infectious complications [5,18,19].

Skeletal muscle weakness in ICU patients is a serious threat for failed weaning from mechanical ventilation and for hampered rehabilitation. Typically, about one third of prolonged critically ill patients develop critical illness polyneuropathy and/or myopathy resulting in important neuromuscular weakness [20]. Theoretically, preventing starvation early during critical illness may partially prevent skeletal muscle catabolism and hereby prevent substantial muscle wasting. However, aggressive nutrition did not effectively reduce muscle breakdown and instead resulted in fat accumulation [21]. Part of the failure to reduce muscle catabolism with PN could be related to the concomitant hyperglycemia as recently shown in an animal model [22,23]. It thus remains unclear whether prevention of hyperglycemia with insulin during early provision of optimal amounts of calories with a combination of EN plus PN, could prevent such complications [15].

### Conflicting guidelines and practices

Current American/Canadian as well as European clinical practice guidelines for nutritional support in the critically ill strongly recommend that EN be used in preference to PN whenever the gastrointestinal tract is intact and functional.

The American/Canadian guidelines in addition recommend that PN should *not *be started at the same time as EN. Also, it is advised that hypocaloric nutrition should be tolerated during the first week in ICU for patients who are not malnourished prior to ICU admission [24,25].

The recent European Society for Parenteral and Enteral Nutrition guidelines for parenteral nutrition in intensive care recommend the administration of supplemental parenteral nutrition within 2 days after ICU admission to patients who cannot be fed sufficiently via the enteral route [26]. Such expert opinion is in part explained by recent data from meta-analyses that revealed a lower mortality with PN in critically ill patients [6].

Current guidelines for nutritional support of patients in the ICU therefore differ substantially among continents and countries. Such differences are explained by absence of high level evidence for either of the strategies applied worldwide and therefore the guidelines are all largely based upon expert opinion. These differences in nutritional practices not only indicate the lack of evidence for impact on patient outcome but also represent important differences in costs for critical care [9,27,28].

### Rationale of the study

In view of the 2 different practice guidelines widely adopted based upon strong expert opinion but in the absence of high level evidence, there is need for an adequately powered randomized controlled trial comparing the two nutritional practices.

In a context of prevention of hyperglycemia and while avoiding overfeeding, a strategy based on early PN completing EN up to a calculated caloric and protein target (further referred to as "early PN") could be superior to withholding PN during the first week of critical illness (further referred to as "late PN") by preventing weakness and enhancing recovery. Alternatively, withholding PN during the first week of critical illness ("late PN") while advocating early EN may shorten ICU and hospital stay by avoiding complications of early PN. Finally, clinical equivalence of the 2 feeding strategies would generate evidence in favor of withholding PN for one week in ICU in view of the cost of this intervention. (Figure 1)

**Figure 1 F1:**
[figure not shown]
**Conceptual cartoon of study design**.

In this randomized controlled study which has the acronym "EPaNIC", we compare "early PN" with "late PN" in ICU patients at risk of developing malnutrition in the ICU. The primary focus of the EPaNIC study is clinical outcome, more specifically the dependency on intensive medical care and need for hospitalization as well as vital status. In addition, a series of mechanistic studies as well as a long-term follow-up is planned. The latter however do not form the basis of this manuscript.

## Methods/Design

### Patient eligibility for inclusion and recruitment

Upon admission to ICU, all adult patients undergo nutritional screening with the Nutritional Risk Screening (NRS 2002) score. This is a scoring system developed to detect the presence of malnutrition and the risk of developing malnutrition in the hospital [29].

All adult patients admitted to any of the 7 participating intensive care units, who present with an NRS score higher or equal than 3, are eligible for inclusion in the EPaNIC study. The following patients are not considered eligible for inclusion: patients with a "do not resuscitate" code at the time of ICU admission, patients expected to die within 12 hours, patients readmitted to ICU after randomization to the EPaNIC trial, patients enrolled in another trial, patients transferred from another ICU after a stay of more than seven days, and patients suffering from ketoacidotic or hyperosmolar coma on admission. Moreover, patients with a body mass index (BMI) <17 (kg/m2), patients with short bowel syndrome treated with home-PN, patients on home mechanical ventilation, pregnant or lactating women are not included. Finally, patients without a clinical indication or with a contra-indication for a central venous catheter and patients who are still able to take oral nutrition on ICU admission or with an NRS score lower than 3 are excluded from this trial.

### Ethical aspects and informed consent

Written informed consent is obtained from the patient or the closest family member or legal guardian. The patient or the next of kin can withdraw from the study at any time, without penalty or impact on treatment.

A register is kept of all patients evaluated for inclusion and of patients who withdraw from the study. The latter are clinically followed up without their data being analyzed in the study.

The study protocol and consent forms were approved by the Institutional Review Board (IRB) of the Katholieke Universiteit Leuven, University Hospitals (approval number ML4190) and by the competent Belgian authorities (EudraCT 2007-000169-40). The Jessa Hospitals' Institutional Review Board IRB (Hasselt) gave positive advice for the addition of 2 of their ICUs (Unit A and C) at the study site Jessa Hospitals.

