#### Blinding of treatment allocation

Treating physicians and patients could obviously not be blinded. However, all outcome assessors, which are investigators not directly involved in the patients care (such as statisticians, laboratory personnel, infectious disease specialists, pathologists, physiotherapists involved in the strength measurement, electrophysiologists) as well as physicians and nurses in the conventional wards, are blinded to treatment allocation.

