#### Data conservation and processing

Data are collected electronically in an anonymized CRF, unambiguously linked to the source file. Data is manually transferred (and checked for accuracy) into the CRF by the clinical research assistance team on a daily basis from the ICU PDMS and the Leuven University Hospitals Clinical Working Station (KWS). Extensive range and consistency checks are performed by the study monitor. Vital status at 90 days will be recorded for all patients, eventually via the Belgian National Registry when this information is not available in the hospital information system.

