### General rules of the statistical analyses

A consort diagram will be reported. (Figure 3) All analyses will be performed on a full intention-to-treat basis. The data file will be finalized 90 days after inclusion of the last patient.

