### Safety endpoints

Safety endpoints comprise vital status (mortality 90 days after randomization independent of ICU and hospital discharge status, hospital mortality, ICU mortality and proportion of patients discharged alive from ICU within 8 days), hypoglycemia, serious adverse events and complications related to the mode of nutrition.

Survival up to 90 days after randomization in both treatment groups will be compared by Kaplan Meier survival plots. The impact of "late PN" versus "early PN" will be analyzed, with and without correction for age, BMI & NRS categories and type and severity of illness, by Cox proportional hazard analysis. Vital status up to 90 days predictably will be traceable for virtually all patients via the National Registry, loss to follow-up will likely not be present except for some patients who will have a residence outside the Belgian territory. In addition, we will record vital status at ICU and hospital discharge and 90 days after randomization, and will analyze differences with Chi-square testing. All analyses will be performed in the intention to treat population. Correction of such differences in ICU and hospital mortality for age, BMI & NRS categories and type and severity of illness, will be performed using a multivariable logistic regression analysis, on condition of the absence of co-linearity between risk factors. Frequencies and percentages for both study arms will be presented together with odds ratios and 95% confidence intervals. As the randomized study intervention only takes place during a time window up to the 8^th ^day in ICU, we also plan to analyze early lethality within this time window in the intention to treat population as part of the safety analysis.

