### Sample size calculation

The sample size was calculated in order to detect, with at least 80% power and 95% certainty, an increase or decrease in average duration of ICU stay with one day [from a baseline assumed ICU stay of 8 ± 13 (mean ± SD) days and a median of 4 days assuming log-normal distribution; power calculated using one-tailed Student's t-test using the mean and SD for an increase and a decrease with 1 day and confirmed with two-tailed Student's t-test after log transformation]. To concomitantly detect with at least 70% power and 95% certainty an ICU mortality increase or decrease of 3% (assuming a baseline mortality of 20% anticipating a Medical-ICU/Surgical-ICU patients fraction of 25/75%; power calculated with two-tailed chi-square testing), a sample of 4640 (patients 2320 per arm) was considered necessary. We plan to calculate the true power of the study for detection of any eventual smaller difference in these outcomes.

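### Excluding the data of patients who withdraw after randomization contradicts the promised full intention-to-treat analysis, and the size of any resulting bias is unknown

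*Protocol article*

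**What the plan says.** All places are in the protocol article.

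- **Ethical aspects and informed consent.** Withdrawal is open throughout: "The patient or the next of kin can withdraw from the study at any time, without penalty or impact on treatment". A register of withdrawals is kept. The rule for these patients is: "The latter are clinically followed up without their data being analyzed in the study".
- **General rules of the statistical analyses.** "All analyses will be performed on a full intention-to-treat basis".
- **Safety endpoints.** The population is restated: "All analyses will be performed in the intention to treat population". On completeness of 90-day vital status the section says that "loss to follow-up will likely not be present except for some patients who will have a residence outside the Belgian territory". Withdrawals are not mentioned there.
- **Data conservation and processing.** "Vital status at 90 days will be recorded for all patients", with the national registry as back-up.
- **Blinding of treatment allocation.** "Treating physicians and patients could obviously not be blinded". Outcome assessors and ward staff are blinded.
- **Sample size calculation.** "a sample of 4640 (patients 2320 per arm) was considered necessary". The mortality part rests on 20% baseline ICU mortality, a 3-point change, at least 70% power and a two-tailed chi-square test.

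**The concern.** A randomized patient whose data are not analysed is outside a full intention-to-treat set. The article states both rules outright, so this is a conflict between two stated rules and not a detail left to a fuller document. Two analysts following the same text could build different primary populations.

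The exclusion depends on something that happens after randomization. Families and treating staff know whether the patient was assigned early parenteral nutrition or a week without it, so the decision to withdraw may depend on the arm and on how the patient is doing. Blinded assessors protect the measurement of outcomes. They do not protect against patients leaving the analysis selectively. The rule reaches every endpoint, including time to discharge alive from ICU and mortality, and the report would carry a population label that its own consent rule makes untrue.

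**Working it through.** **1. The passages side by side.** The consent section drops the data of anyone who withdraws, at whatever time. The statistical section keeps everyone randomized. The article defines no modified intention-to-treat set. It does not distinguish a patient who stops the intervention from one who refuses use of data, and it states no sensitivity analysis for withdrawals. Recording 90-day vital status for all patients also fits badly with a rule that would leave part of it unused.

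**2. The plan's own figure.** For ICU mortality of 20% against 23%, two-sided 5%, 70% power and pooled variance:

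n per arm = [1.960·√(2·0.215·0.785) + 0.524·√(0.20·0.80 + 0.23·0.77)]² / 0.03² ≈ 2315

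This agrees with the planned 2320. Power at 2320 per arm is 70.1%, so there is almost no reserve.

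**3. Loss of power.** The document gives no withdrawal rate, so these rates are assumed and applied to both arms.

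| Withdrawn | Left per arm | Power, 20% to 23% |
|---|---|---|
| 0% | 2320 | 70.1% |
| 1% | 2296 | 69.7% |
| 2% | 2273 | 69.2% |
| 5% | 2204 | 67.9% |

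The loss is minor. Bias is the main issue.

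**4. Bias from one-sided withdrawal.** Assume true ICU mortality of 20% in both arms, a fraction w withdrawing from one arm only, and mortality m among them. The observed mortality in that arm is (0.20 − w·m)/(1 − w).

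- w = 1%, m = 0: 0.20/0.99 = 20.2%, a shift of +0.2 points.
- w = 1%, m = 40%: 0.196/0.99 = 19.8%, a shift of −0.2 points.
- w = 2%, m = 0: 0.20/0.98 = 20.4%, a shift of +0.4 points.
- w = 2%, m = 40%: 0.192/0.98 = 19.6%, a shift of −0.4 points.

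The standard error of the difference is √{0.16·[1/2320 + 1/(2320·(1 − w))]}. At w = 2% this is 0.0118, and the shift is 0.0041/0.0118 ≈ 0.35 standard errors. The chance of a significant result under no true difference is then about 6.4%, against about 5.3% at w = 1%. At w = 5% the shift is 1.05 points and the error about 14%.

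**5. The extreme.** Suppose that 15 to 93 patients withdraw (0.33% to 2% of 4640, an assumed range), all from one arm, and that all of them die. That arm would have 0.20 × 2320 = 464 deaths. Exclusion removes the patients from numerator and denominator.

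- 15 patients: (464 − 15)/(2320 − 15) = 449/2305 = 19.48%, a shift of 0.5 points.
- 93 patients: (464 − 93)/(2320 − 93) = 371/2227 = 16.66%, a shift of 3.3 points.

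The design difference is 3 points.

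**The case against.** The rule stands in the consent section, and the protocol and consent forms were approved by the review board and the competent authorities. It may therefore reflect withdrawal of consent to use data, which the trial may not be free to override. The article does not say so, but the possibility stands, and it limits the remedy. It does not rescue the label: a set without those patients is still not full intention-to-treat.

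Transparency is partly provided for. A register of withdrawals is kept and a CONSORT diagram is promised, which is the usual place to show exclusions by arm. This makes the problem visible but does not settle which patients are analysed.

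On size, a reader might take the upper extreme to mean that withdrawal could overturn the mortality result. The documents do not support that. The extreme needs 93 withdrawals in one arm (4% of it), none in the other and death in every case, and nothing in the article points to such a rate or pattern. Dividing 93 by 2320 would even suggest 4.0 points, but that leaves the excluded patients in the denominator.

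A reader might also infer a withdrawal rate from the interim analysis, which was planned after patient 1500 left the ICU and used 1495 patients. The article gives no reason for the gap of 5, and incomplete outcomes could explain it equally well. The figure of 15 (5/1500 × 4640) therefore serves only as the low end of an assumed range.

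**Conclusion.** The contradiction is real and does not depend on how many patients withdraw: the consent section excludes data that the statistical section says will be analysed.

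The bias is a possibility whose size cannot be known from the article. Under one-sided withdrawal of 1% to 2% of an arm, with 0% or 40% mortality among those withdrawing and 20% true mortality in both arms, it is about 0.2 to 0.4 points, and the nominal 5% error rises to about 5.3% to 6.4%. It is small if withdrawal is rare or balanced. Only a deliberately extreme assumption brings it to 3.3 points. These figures concern ICU mortality; the effect on time to discharge alive was not quantified.

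The point should be fixed because it concerns who is in the primary analysis. Its likely size does not make it critical.

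**What to change.** Reconcile the sections on consent, data conservation, general rules of analysis and safety endpoints as follows.

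- Separate withdrawal from the intervention from refusal of data use.
- Analyse, in the randomized arm, all data collected up to withdrawal, and registry vital status at 90 days where consent and law allow.
- Exclude data only where their use is refused.
- Report withdrawals and exclusions per arm.
- Add a sensitivity analysis, for example best and worst case for mortality. Censoring time-to-event outcomes at withdrawal is not enough alone, because withdrawal may be related to prognosis and to arm.

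If the approved consent requires exclusion, stop describing the population as full intention-to-treat, and keep the per-arm reporting and the sensitivity analysis.

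The cost is an amendment to the wording with ethics review, and a little more analysis. Ethics review is needed because analysing these data departs from the approved rule. How much is recoverable is uncertain: the article promises clinical follow-up after withdrawal, which need not mean that case report form data continue to be collected. The data file is finalized 90 days after the last inclusion, so the rule should be settled before then.

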### Data collected at study entry

At baseline, data on demographic and clinical characteristics of the patients are obtained. Disease specific risk scores are calculated and co-morbidities and known use of important medications prior to admission are noted: these comprise, among others, Acute Physiology and Chronic Health Evaluation II score (APACHE II), presence of cancer, diabetes mellitus, kidney failure (Chronic Kidney Disease score), liver failure (Child classification), COPD (Gold classification), and heart failure (New York Heart Association Functional Classification ≥ 2). Sepsis upon admission is labeled as such using modified Bone criteria [30,31].

